### Sample size

The aim of the YOD-RiSoCo study is to aid in the diagnosis of YOD by improving measurement of social cognition. Therefore, the main outcome measure is the difference between bvYOD patients and healthy controls in performance on the new SC instruments. This way we hope to differentiate pathology in bvYOD from healthy controls and to prove the sensitivity of the instruments for the specific pathology.

The estimated effect size is based on a previous study assessing the sensitivity of a new social cognition task [27]. In this study, significant differences were found between patients and controls in performance on the SNQ-NL Total score, with a large effect size (η_p_^2^ = 0.23). However, considering that no studies have yet been conducted with the current measurements and in the current population, a moderate effect size of 0.5 (default option) for the power calculation was chosen.

The power calculation was performed with *G*Power 3.1* [28]. For achieving 80% power, with 20% chance for making a Type II error and a 5% significance, the estimated sample size per group is 64. If the required number of approximately 128 inclusions is still not achieved within 24 months, the inclusion period will be extended with 6 months. In case of missing data, we will include additional subjects to reach the target N.

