**Methods:**

The YOD-RiSoCo study is an observational prospective cohort study, consisting of two separate, but related, studies. Study 1 includes 64 patients with bvYOD and 64 healthy controls to assess the sensitivity and validity of newly developed SC instruments for measuring emotion experience and empathy, by comparing their average group performance. Furthermore, validity of the new instruments will be assessed by analysing the associations of performances on these new tests with those on more traditional SC and other neurocognitive tests. Study 2 focuses on assessing to which extent SC measures relate to risk-taking behaviour. This study includes 20 patients with bvYOD and 20 healthy controls from Study 1, in addition to 20 patients with non-bvYOD (e.g. Alzheimer’s dementia or vascular dementia) and 20 patients with serious brain injury affecting frontal networks. A specific question is whether the relationship between SC and risk-taking behaviour is generic (for all groups with SC impairments), or specific (not in dementia without SC impairments).

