1)Assess sensitivity of new performance-based SC measures (including emotion experience and empathy) ◊ Study 12)Assess construct validity of the new performance based SC measures ◊ Study 13)Assess the relationship between social cognition and unsafe risk-taking behaviour (measuring ecological validity of the new SC tests), and investigate if this relationship is generic (by including patients with brain injury affecting frontal networks) or specific (by including patients with non-bvYOD variants, for whom no SC impairments or risk-taking behaviour are expected) ◊ Study 2

As a result of this study, we hope to introduce new, sensitive neuropsychological instruments which may aid in a more timely diagnosis of bvYOD and a better identification of social behavioural symptoms in general.

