#### Study 1 New SC instruments.

Independent samples t-tests (or a non-parametric alternative, such as chi-square or Mann-Whitney U tests) will be performed to assess if the newly developed tasks can differentiate patients with bvYOD from healthy controls, based on social cognition, on a group level.

Construct validity of the newly developed measures will be assessed with parametric (such as Pearson’s correlation), or if more appropriate, non-parametric (such as Spearman’s) correlation analyses between the newly developed SC instruments, and existing SC instruments and other cognitive tests, respectively. It is expected that the new SC tests are significantly correlated to existing SC tests, indicating that the tests fall within the SC domain (convergent validity). However, no high correlation is expected, as the new tests measure different aspects of SC. No significant correlations are expected between the new SC tests and other cognitive measures (such as memory and attention), indicating that the tests measure SC specifically and no other cognitive domains, such as memory and attention (divergent validity).

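### A group-level patient–control difference is said to prove the sensitivity of tests meant to aid diagnosis, but it shows known-groups validity only

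*Protocol article*

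**What the plan says.** All references are to the protocol article. The Background lists assessing the sensitivity of the new performance-based measures as the first aim. Under Sample size, the purpose of the study is "to aid in the diagnosis of YOD by improving measurement of social cognition", and from this the article derives that "the main outcome measure is the difference between bvYOD patients and healthy controls in performance on the new SC instruments". It then adds: "This way we hope to differentiate pathology in bvYOD from healthy controls and to prove the sensitivity of the instruments for the specific pathology".

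The analysis is under Statistical analysis, Study 1: "Independent samples t-tests (or a non-parametric alternative, such as chi-square or Mann-Whitney U tests) will be performed", to see whether the new tasks "can differentiate patients with bvYOD from healthy controls, based on social cognition, on a group level". The Methods paragraph of the Abstract agrees: sensitivity and validity are assessed "by comparing their average group performance". The correlation analyses in the Study 1 section serve construct validity, which is a separate aim.

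The Discussion paragraph of the Abstract says that the results will yield sensitive tests that may contribute to earlier diagnosis. The main Discussion repeats this.

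**The concern.** A significant difference in group averages shows that patients as a group score differently from controls. It does not say what share of patients a test identifies, or what share of healthy people it would wrongly flag. Two heavily overlapping distributions can differ significantly once the groups are large enough.

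The article moves from the first kind of statement to the second without an estimate that supports the step. At stake is the main conclusion of Study 1. If the main outcome is significant, the stated reasoning would allow an instrument to be called sensitive, in support of diagnosis, whatever its ability to separate individuals.

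**Working it through.** **Inputs from the article.** Effect size 0.5, read as Cohen's d; 64 per group; 80% power; two-sided alpha 0.05; Bonferroni-Holm or another suitable correction for multiple comparisons; partial eta squared 0.23 in the earlier study of another task.

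**Assumptions not in the article.** Normal scores with equal SD in both groups; specificities of 80%, 90% and 95%; three new instruments (the number listed in Table 1) for the Holm step; two equal groups without covariates when converting eta squared.

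**1. The plan's own figure.** For a two-sample t-test with d = 0.5 and n = 64 per group, the noncentrality is 0.5 × √(64/2) = 2.83 and the critical t on 126 df is 1.979. Power is 0.801; at 63 per group it is 0.795. The stated 64 per group reproduces, so the sample size is right for a mean difference.

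**2. What a given d means for individuals.** Under the equal-variance normal model:
- AUC = Φ(d/√2)
- sensitivity at specificity s = Φ(d − z_s), with z_s = 0.842, 1.282 and 1.645 at 80%, 90% and 95%.

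At d = 0.5, AUC = Φ(0.354) = 0.638. Sensitivity is Φ(−0.342) = 36.6%, Φ(−0.782) = 21.7% and Φ(−1.145) = 12.6%. At the cut-off where sensitivity equals specificity, both are Φ(0.25) = 59.9%.

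**3. The smallest difference that would be significant.**
- Unadjusted: d = 1.979 × √(2/64) = 0.350.
- Strictest Holm step with three instruments, two-sided alpha 0.05/3: critical t = 2.426, so d = 2.426 × √(2/64) = 0.429.

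| Observed d | AUC | Sens. at 80% spec. | at 90% | at 95% |
|---|---|---|---|---|
| 0.350 (just significant, unadjusted) | 0.60 | 31% | 18% | 10% |
| 0.429 (strictest Holm step) | 0.62 | 34% | 20% | 11% |
| 0.5 (planning value) | 0.64 | 37% | 22% | 13% |
| 1.093 (from eta squared 0.23) | 0.78 | 60% | 43% | 29% |

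The last row uses d = 2 × √(0.23/0.77) = 1.093.

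**4. What the same data can deliver.** With 64 per group and AUC A = 0.638, the Hanley–McNeil variance uses Q1 = A/(2 − A) = 0.469 and Q2 = 2A²/(1 + A) = 0.497:

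SE = √{[A(1 − A) + 63(Q1 − A²) + 63(Q2 − A²)]/64²} = 0.049.

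The 95% CI is 0.638 ± 1.96 × 0.049, about 0.54 to 0.73. At AUC 0.80 the half-width is about 0.08. An observed sensitivity of 51/64 (80%) at a fixed cut-off would have an exact 95% CI of about 68% to 89%.

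**The case against.** **The word may be meant in a weaker sense.** The article partly uses sensitive to mean responsive to a patient–control difference. The Study 1 analysis text is limited to group level, and the description of the Groningen ToM battery selects its most sensitive items by the size of a group difference. This stands in part: on that reading the t-test is the right test. It does not rescue the Sample size section, which ties proving sensitivity to diagnosis, or the conclusions in the Abstract and Discussion.

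**An article may leave ROC analysis and cut-offs to the full protocol or analysis plan.** That is right, and their absence alone is no fault. The fault is an inference that the article does state.

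**The accuracy figures rest on assumptions.** A reader might infer that the plan would certify a test that detects one patient in five. The documents do not support that as a property of the plan. The figure needs 90% specificity, which appears nowhere in the article, and equal-variance normal scores, although the ETIF subscales are bounded at 12 and the article foresees non-normal data. If the patient SD were 1.5 or 2 times the control SD, with d = 0.5 on the root-mean-square SD, sensitivity at 90% specificity would be about 33% or 40%. The AUC would still be 0.64. Also, 0.5 is a deliberately cautious default, not a forecast; the earlier effect was described as large.

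**The tests are meant as an aid.** Diagnosis in this study rests on an interdisciplinary consensus using several sources, so stand-alone accuracy is not the only standard. This stands, and it argues against demanding a particular AUC.

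**Conclusion.** The planned group comparison is valid and correctly sized for known-groups validity. What does not follow is the step from a significant difference to proven sensitivity of instruments meant to aid diagnosis. Under equal-variance normal scores, the planning effect corresponds to AUC 0.64 and to sensitivity between 37% and 13% over assumed specificities of 80% to 95%. A just-significant result corresponds to 18% at 90% specificity, or 20% at the strictest Holm step with three instruments.

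Two stronger readings are tempting and should be resisted. One is that the t-test is the wrong analysis; it is the right one for a group difference. The other is that the article sets a success criterion that a useless test could pass; it sets no formal threshold and expresses a hope. Severity is moderate: design, sample size and data collection are unaffected, but the wording of the main conclusion is.

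**What to change.** 1. Keep the comparison of means, and name it group-level discrimination (known-groups validity).
2. For each new instrument, report the AUC with 95% CI. The Mann-Whitney test that the article already allows gives the estimate directly, as U/(n₁n₂).
3. Report sensitivity with CI at a specificity fixed before the data are analysed. Take the cut-off from the control distribution (for example its 5th or 10th percentile, with adjustment for age and education if needed), not from the best split of the same data.
4. Base any statement that an instrument is sensitive on those estimates. If they are not added, remove the statement that the group difference proves sensitivity, and tone down the conclusions in the Abstract and Discussion to match.

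A minimum AUC stated in advance is optional.

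The cost is a little more analysis and some rewording; no new participants or measurements are needed. The downside for the authors is that a significant mean difference alone would no longer support the word sensitive. Recruitment is planned to the end of 2026, so the specificity and the cut-off rule can still be set before analysis.

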## Methods and materials

### Study design study 1

Study 1 of the YOD-RiSoCo study is an observational prospective cohort study, that aims to include 64 patients with bvYOD and 64 healthy controls. Controls will be matched to patients on a group level, so that sex, age, and educational level distributions do not significantly differ between groups. The recruitment of controls will be adapted to match the included patients.

### Study design study 2

Study 2 of the YOD-RiSoCo study is an observational study that aims to include 20 patients with bvYOD, 20 healthy controls, 20 non-bvYOD patients and 20 patients with brain injury affecting frontal processes. The bvYOD and healthy control patients will be included from Study 1 (Fig 1).

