**New social cognition measures**	
Nummenmaa Emotion Experience Test (NEET)	Bodily experience of emotions
Empathy Task of Identifying emotions and Feeling with another (ETIF)	Empathy; identifying emotions and feeling with another
Groningen Theory of Mind Battery	Cognitive and affective Theory of Mind, verbally as well as non-verbally

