### Statistical analysis

The analyses will be conducted in Statistical Package for the Social Sciences (SPSS). Assumptions for the intended analyses will be checked. Parametric tests will be used for normally distributed data, otherwise a non-parametric alternative will be used. For all analyses, the alpha will be set at 0.05, and analyses will be two-sided. In case of multiple comparisons, Bonferroni-Holm correction, or another appropriate correction, will be applied. Demographic variables will be analysed on a descriptive level (mean, standard deviation, frequency, percentage). To ensure matched groups of patients and controls, comparisons will be made on demographic variables with t-test (or non-parametric tests such as chi-square or Mann-Whitney U tests). Potential confounders will be included as covariates.

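### The stated 80% power is for one t-test at unadjusted alpha, while the main outcome covers three new instruments under a multiplicity correction; at d = 0.5 per-instrument power under Holm is about 66% to 75%.

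*Protocol article*

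**What the plan says.** All references are to the protocol article.

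- **Main outcome (Sample size):** "the main outcome measure is the difference between bvYOD patients and healthy controls in performance on the new SC instruments". The outcome is plural and no instrument or score is singled out.
- **Number of instruments (Table 1, new social cognition measures):** three, namely the "Nummenmaa Emotion Experience Test (NEET"), the Empathy Task of Identifying emotions and Feeling with another (ETIF) and the Groningen Theory of Mind Battery.
- **Test (Statistical analysis, Study 1):** independent-samples t-tests on the new tasks, or a non-parametric alternative.
- **Error rate (Statistical analysis):** "For all analyses, the alpha will be set at 0.05, and analyses will be two-sided".
- **Multiplicity (Statistical analysis):** "In case of multiple comparisons, Bonferroni-Holm correction, or another appropriate correction, will be applied".
- **Sample size:** "a moderate effect size of 0.5 (default option) for the power calculation was chosen", and then "For achieving 80% power, with 20% chance for making a Type II error and a 5% significance, the estimated sample size per group" is 64.
- **Allocation (Study design study 1):** Study 1 "aims to include 64 patients with bvYOD and 64 healthy controls".

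**The concern.** The sample size calculation and the multiplicity rule do not use the same significance level. The calculation spends the whole 0.05 on one comparison. The main outcome involves three comparisons of equal standing, and the general rule says multiple comparisons are corrected. Under Holm, an instrument may have to reach 0.05/3 before it counts as significant, and the calculation makes no allowance for that.

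An instrument with exactly the planned effect would then be missed with a probability of about 25% to 34%, not the 20% stated. The Sample size section gives proving the sensitivity of the instruments as the aim, so the power of each instrument matters. With no primary score named, it is also unclear whether the 80% refers to one given instrument, to any of them or to all of them, and these probabilities differ widely.

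**Working it through.** **Inputs.** Effect size 0.5, read as Cohen's d; 64 per group, 1:1; alpha 0.05 two-sided; 80% power (Sample size, Study design and Statistical analysis sections). Three instruments (Table 1). The correlation between instruments is not given, so a range of 0 to 0.5 is assumed.

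**Step 1. Reproduce the stated figure.** For a two-sample t-test with n per group, df = 2n − 2 and the noncentrality is d × √(n/2). Power is the probability that a noncentral t variable exceeds the two-sided critical value in absolute size.

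- n = 64: df = 126 and noncentrality = 0.5 × √32 = 2.83.
- Alpha 0.05: critical value 1.98, power 80.1%. With 63 per group, power is 79.5%, so 64 is the smallest size that reaches 80%.
- A one-sided test would need 51 per group, which does not match.

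The stated 64 is therefore the size for a single two-sided test at the full 0.05, with nothing set aside for multiplicity.

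**Step 2. One given instrument at the first Holm threshold.** Alpha = 0.05/3 = 0.0167, critical value 2.43, same noncentrality 2.83.

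- Power = 65.6%.
- Effect detectable with 80% power at 64 per group: d = 0.58.
- Size that would restore 80% at d = 0.5: 86 per group (172 in total).

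If the family were only two instruments (alpha 0.025), power would be 71.2% and 78 per group would be needed. The shortfall does not depend on counting exactly three.

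**Step 3. The full Holm procedure.** The 65.6% is a floor, because Holm relaxes the threshold to 0.025 and then 0.05 as other instruments are rejected. Simulation with three instruments, 64 per group:

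| Situation | Quantity | Correlation 0 | 0.3 | 0.5 |
|---|---|---|---|---|
| All three differ by d = 0.5 | average power per instrument | 75% | 74% | 74% |
| All three differ by d = 0.5 | all three significant | 50% | 55% | 59% |
| All three differ by d = 0.5 | at least one significant | 96% | 91% | 87% |

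If only one instrument truly differs, by 0.5, its simulated Holm power is about 66%, in line with step 2.

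**Step 4. Sensitivity to the true effect.** Power for one instrument at alpha 0.0167 with 64 per group is 75% at d = 0.55, 83% at 0.6, 94% at 0.7 and 98% at 0.8. The benchmark cited in the Sample size section is a partial eta-squared of 0.23. Treating it as a simple comparison of two equal groups (an assumption), f = √(0.23/0.77) = 0.547 and d = 2f = 1.09, where power exceeds 99%.

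**The case against.** **The arithmetic is correct as stated.** It is: 64 follows from the inputs given. The problem is that those inputs do not match the corrected analysis of a plural main outcome.

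**The family is inferred.** The multiplicity sentence is a general one and allows another correction. The instruments measure different aspects of social cognition, so separate claims at 0.05 each could be defended, and on that reading 80% holds for each. A later analysis plan may also define the family. This lowers the weight of the point but does not remove it. The article itself sets out several co-equal comparisons, a correction rule and a power figure, and the figure holds only if the rule is not applied to those comparisons.

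**The planning effect is conservative.** This stands, and step 4 shows the margin. The Sample size section nevertheless set the benchmark aside because it came from other measures and another population, so the margin cannot be relied on. The stated power should hold at the value actually chosen.

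**Stronger readings that the document does not support.** A reader might infer that the study has only a 66% chance of a positive first Holm step. That is wrong: 66% is the power of one given instrument at alpha/3, and if all three differ by 0.5 the first step rejects something with probability 87 to 96%. A reader might also count the ETIF subscales and total and the four parts of the Theory of Mind battery as separate tests, and so arrive at a family of eight with much lower power. The article nowhere says eight tests will be run. It speaks of testing the tasks, and the ETIF total is simply the sum of its two subscales.

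**Conclusion.** The point holds in a limited form. The 80% applies to one two-sided test at 0.05. Under Holm across three instruments at d = 0.5 and 64 per group, power per instrument is about 66% at the floor and about 74 to 75% on average when all three differ. The overstatement is thus roughly 5 to 14 percentage points per instrument.

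This rests on one main score per instrument, approximately normal scores, Holm as the correction used, and correlations between instruments of 0 to 0.5. It does not show that the study is too small to be useful: an effect of about 0.58, only slightly above the planned 0.5, is detectable with 80% power even at alpha/3. It should be fixed, but it does not threaten the study.

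**What to change.** Add one or two sentences to the Sample size section, leaving the sample size unchanged:

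- State that the family for the main outcome is one named main score from each of NEET, ETIF and the Groningen Theory of Mind Battery, tested under Bonferroni-Holm at an overall two-sided 0.05.
- Restate the power: with 64 per group and d = 0.5, about 66% (floor) to 75% per instrument, with 80% at alpha/3 for d of about 0.58.

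The cost is a less favourable power statement.

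An alternative is to name a single primary score and test it at 0.05, which makes the 80% true for that score. This is the sponsor's choice, because it has a price. If the other two follow in fixed order and all effects are 0.5 (correlation 0 to 0.5), the second instrument has about 64 to 69% power and the third about 51 to 61%. The later claims would also depend on the first result, although the instruments measure different constructs.

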### Ethics approval and consent to participate

YOD-RiSoCo will be conducted according to the principles of the Declaration of Helsinki and the national and international standards of Good Clinical Practice. Potential participants receive detailed written and oral information on the study procedures and all participants will provide written informed consent. Ethical approval of the study protocol was obtained from the Medical Ethical Committee of the UMCG (2024/395). The YOD-RiSoCo study protocol is registered at clinicaltrials.gov, with identifier NCT06286293.

## Results

Recruitment started from January 2025 and is planned to continue until the end of 2026. The first publications are expected in early 2027.

## Discussion

To the best of our knowledge, the YOD-RiSoCo study will be the first to investigate the relationship between aspects of social cognition and risk-taking behaviour in a broad sample of patients with bvYOD, non-bvYOD, patients with brain injury affecting frontal networks, and healthy controls. Furthermore, we hope the study will lead to new valid instruments for measuring aspects of social cognition for which currently valid instruments are lacking.

First, the YOD-RiSoCo study will result in new sensitive and valid measures for aspects of SC, such as bodily emotion experience, and empathy. These measures will hopefully facilitate a better identification and deeper understanding of social cognitive difficulties in patients with behavioural variants of young-onset dementia. As patients with these bvYOD subtypes present with changes in social behaviour, related to SC impairments, the new instruments will hopefully lead to better recognition of these first symptoms, resulting in a timelier diagnosis.

Furthermore, by investigating the relationship between social cognition and risk-taking behaviour, the association between SC impairments and problematic social behaviour, such as risk-taking behaviour, will be assessed. Identifying risk-taking behaviour is important, as it can have detrimental consequences for patients themselves, but also for other people that might be unintentionally affected by risk-taking behaviour. If a relationship between SC and risk-taking behaviour is found in this study, guidelines regarding fitness to drive in patients with bvYOD or brain injury affecting frontal processes should be reviewed and revised to be more applicable to patients with SC impairments and social behavioural change.

In conclusion, the results of the YOD-RiSoCo study will contribute to a more comprehensive understanding of social cognition and risk-taking behaviour in patients with young-onset dementia, which may speed up the diagnostic process of young-onset dementia, allowing timely provision of appropriate counselling and care for patients and their close others.
